### Ethics approval

Ethical approval for the study was received from the Joint Chinese University of Hong Kong – New Territories East Cluster Clinical Research Ethics Committee (2018.469). Approval was also obtained from the hospital. The study will be compliant with the Declaration of Helsinki. Protocol modifications will be communicated to the ethics committees.

### The nurse-led eHealth cardiac rehabilitation program

The NeCR program is a health technology based CR program which aims to optimize positive behavioral changes and health outcomes of patients who are discharged following a CHD event. The intervention will be delivered by a cardiac nurse who has extensive experience in clinical teaching and patient education, using a hybrid approach in two phases: i) a brief face-to-face preparatory phase; and, ii) the CR program delivered by health technology using an empowerment approach. Since CR uses a multidisciplinary approach, cardiologists, cardiac nurse, physiotherapist and dietitian were involved in designing the content of the eHealth CR program. A nurse-led approach is used as the cardiac nurse plays a prominent role in supporting patient empowerment and health behavioral changes [40]. Nurses are effective in coordinating care with other health disciplines in rehabilitative services [41]. In implementing the eHealth CR program, the nurse researcher will coordinate the care and seek consultation with the involved disciplines if necessary to optimize the participants’ outcomes. The intervention content is based on updated international guidelines and culturally appropriate national recommendations for CR [42–49].

### Face-to-face preparatory phase

The preparatory phase will be conducted by the nurse researcher prior to the participant’s discharge. It consists of two sessions, with the first session being an individualized health counseling session and the second as a group-based engagement session.

The aim of the individualized health counseling is to identify patients’ self-care needs through a health assessment, develop client-centered goals and a corresponding action plan for lifestyle modification and disease management. The assessment focuses on self-care behaviors for managing CHD including exercise pattern, dietary habits, stress management and tobacco cessation as well as social aspects of disease management such as demographic background, role demand and social support to identify self-care needs. Patients’ function capacity will be assessed by submaximal test using remote electrocardiography (Mindray Tel-200, China) monitored six-minute walk test, based on which the metabolic equivalent (MET) will be calculated by the nurse [46, 50]. Accordingly, the nurse will provide brief health counseling based on the international guidelines recommendations for CR. The discrepancy between the patients’ self-reported behaviors and the guideline recommendation will be highlighted, and the impact of this on health outcomes will be elaborated upon. By increasing the participants’ awareness of their own self-care deficits, the nurse will support them in developing their goals for improving exercise patterns, dietary behaviors, and stress management.

The goal setting for exercise will indicate the frequency, duration, and intensity of exercise to gradually achieve at least 150 min of moderate weekly exercise. The nurse will also teach the participants about using Borg’s ratings of perceived exertion to achieve the desired intensity with a perceived exertion of 12 to 14 (“somewhat hard” on a scale of 6 to 20) [51]. For dietary habits, a guideline based culturally appropriate 10-item dietary habit checklist has been developed assessing food intake, cooking methods, eating pattern, and method of eating in restaurants. This checklist is adapted from the dietary checklist designed by the Department of Health in Taiwan to guide the dietary modification for cardiac patients [52]. The research team has modified the content so as to make it culturally relevant to the CHD patients in China. The revised content has been validated by two Chinese dietitians. Participants will be supported in setting successive goals to eventually attain over 90% adherence to this checklist. As for stress management, participants will be supported to set goals of managing stress below a level of 3 as assessed by 0–9 scored scale [53]. The nurse will collaborate with the patients to work out the action plan with a variety of exercise, dietary and relaxation skills options. Participants who smoke will also be supported to set a cessation goal and provided with tips such as nicotine replacement therapy, avoid smoking for social influences and managing stress [54]. A written participant-centered goal-driven action plan and information handout for self-management will be provided to reinforce knowledge retention. The individualized goals and action plan will be uploaded to the participants’ password protected personal webpages on the eHealth CR platform.

The group-based engagement session will take place in the hospital meeting room with 4~6 participants per group. The aims are: i) orientate participants to the operation of the web- and tele- platform, and ii) form a cohesive peer support group to optimize lifestyle behavioral changes. The nurse will share anonymously the goals of the participants and discuss the importance of goal attainment in optimizing health outcome. The nurse will give an orientation to the web-platform by demonstrating each key feature and distribute the e-platform user manual. In order to ensure the success of the subsequent self-monitoring on physical exercise, a pedometer with written instructions, will be provided. Practice and return demonstration is needed to ensure skill mastery. Finally, the nurse will invite participants to enter a WeChat telecare platform consisting of 12 ~ 16 participant members.

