#### Self- monitoring with motivational feedback platform

The self-monitoring page will document the goals and action plans developed for improving exercise level, dietary habits, stress management and/ or tobacco cessation during the preparatory phase. Participants are recommended to input self-monitoring data on a daily/weekly basis to indicate the level of goal attainment. For exercise, participants will upload exercise times, the intensity level as light/moderate/vigorous and the duration of engagement in 1 week. In addition, the guidelines for CR also recommend a higher level of walking to exceed 7000 steps [56], and each participant will be encouraged to upload their daily step count measured by their pedometer. Participants will be encouraged to complete the guideline based dietary habit checklist and their score on the 0 to 9 stress scale to indicate their dietary habit and stress level. A traffic light system will be used to give motivational feedback based on the level of goal attainment, with red indicating attention required (< 50% of goal attainment), yellow representing moderate achievement (> 50–90% of goal attainment) and green indicating full attainment (90–100% of goal attainment). An automated message which corresponds to the level of goal attainment and shares the trend in participants’ recordings will be presented. Patients will be asked to report on tobacco use and encouraged to update their smoking status (if applicable) with green indicating they have quit while red represents smoking. Based on the pre-determined coding, an overall score on goal attainment will be generated along with the traffic light system to reflect progress on each behavioral change.

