#### Tele-care platform

In the tele-care platform, the nurse will retrieve self-monitoring data uploaded by participants and anonymously share goal attainment of group members as well as discuss their experiences and address any concerns. Reminders for uploading data will be sent to participants weekly. This platform permits participants to contact the nurse about issues or adverse changes in health. The nurse will contact each individual at weeks 2 and 4 post-discharge to assess fitness, explore difficulties, encourage progress and offer solutions. This may lead to revision of the action plan or goal adjustment. Participants will be asked to maintain password and account security, and to avoid discussing of intervention content with other patients in the hospital to avoid contamination.

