### Usual care

Participants in the both groups will receive the usual health care information related to maintaining a healthy lifestyle (exercise, diet and smoking cessation), instructions on medication during hospitalization, and one follow-up call. The research nurse will instruct control group participants on use of the pedometer.

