### Primary outcomes

The primary outcomes focus on health behavioral change including physical activity, health promoting lifestyle habits, and smoking behaviors. Physical activity is defined as movement of the body that uses energy. Objectively, physical activity level will be measured by the pedometer (Mi Band, China) record of step count for three weekdays [57]. A pedometer correlates strongly with different accelerometers (median r = 0.86) as well as the time in observed activity (median r = 0.82) [58]. The International Physical Activity Questionnaire (IPAQ) will be used to comprehensively assess the self-reported time spent in walking, light/moderate/rigorous exercise and sitting across various domains using 27 items. The IPAQ has test–retest reliability with intra-class correlation coefficients of 0·74 to 0·97 for each sub-domain for Chinese adults [59]. Total physical activity measured by the IPAQ was moderately correlated with pedometer measured exercise levels (r = 0.46) [60].

Health promoting behaviors will be measured by the Health Promoting Lifestyle Profile II (HPLP- II) [61]. The HPLP- II measures six aspects of health promotion behaviors including nutrition, interpersonal support, stress management, exercise, health responsibility and self-actualization. The HPLP - II has good internal consistency with 0.92 for the entire scale and 0.69–0.84. The HPLP uses a four-point scale with 1–4 representing always to never with a total score ranging from 40 to 160 and a higher score indicating better health behavior. The HPLP-II has been translated and validated into Chinese with Cronbach’s α coefficient of 0.63 to 0.81 [62].

Smoking status will be asked to evaluate the abstinence rate using two questions: (1) what is your current smoking status? (current smoker, ex-smoker or nonsmoker) (2) How many cigarettes do you smoke per day? [63].

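### The Mi Band is both a NeCR self-monitoring tool and the only objective primary measure, and its handling as described differs by arm, so more complete recording in NeCR could look like a step-count benefit

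*Protocol article*

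**What the plan says.** All references are to the protocol article.

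- **Outcome (Primary outcomes).** The objective measure is defined thus: "physical activity level will be measured by the pedometer (Mi Band, China) record of step count for three weekdays". The other primary measures (IPAQ, HPLP-II and two smoking questions) are self-reported.
- **NeCR, training (Face-to-face preparatory phase).** To support later self-monitoring of exercise, "a pedometer with written instructions, will be provided". The next sentence reads: "Practice and return demonstration is needed to ensure skill mastery".
- **NeCR, ongoing use (Self-monitoring with motivational feedback platform; Tele-care platform).** In addition to exercise logging, "each participant will be encouraged to upload their daily step count measured by their pedometer", within a platform that returns traffic-light feedback on goal attainment. "Reminders for uploading data will be sent to participants weekly". There is also individual contact: "The nurse will contact each individual at weeks 2 and 4 post-discharge to assess fitness".
- **Control (Usual care).** "The research nurse will instruct control group participants on use of the pedometer". Both arms receive usual care, which includes "instructions on medication during hospitalization, and one follow-up call".
- **Both arms (Secondary outcomes).** The outcome assessor calls monthly about unplanned use of health services. The call is not described as touching on the band.

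**The concern.** One device serves two purposes. In NeCR it is part of the treatment; in both arms it is the measuring instrument. When the treatment includes training and repeated engagement with the instrument, the completeness of the recording can depend on the arm. A band that is off the wrist or wrongly used undercounts. NeCR participants have a standing reason to keep it on, because their uploads feed a visible score. No counterpart is described for controls.

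The error would favour NeCR, and other features of the plan do not remove it:

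- Blinding of the outcome assessors does not help, because the undercount arises before anyone reads the record.
- Adjustment for baseline does not help, because baseline data are collected before allocation and the difference in handling follows it. The error would go straight into the GEE comparison of the arms over time.
- The IPAQ is a limited cross-check. It is self-reported, and the article puts its correlation with pedometer-measured exercise at r = 0.46.

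**Working it through.** **1. Handling of the band, arm by arm, as described**

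| Element | NeCR | Control |
|---|---|---|
| Instruction on the band | Yes | Yes |
| Written instructions | Yes | Not mentioned |
| Practice with return demonstration | Yes | Not mentioned |
| Daily step upload encouraged, with feedback | Yes | Not described |
| Weekly reminder | To upload data | Not described |
| Other contact | Nurse at weeks 2 and 4; usual-care call; monthly assessor call | Usual-care call; monthly assessor call |

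The arms share basic instruction. The difference is one of degree at training and clearer afterwards.

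**2. The plan's own figure**

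Inputs from Study sample and Data analysis: d = 0.5, 80% power, two-sided 5%, attrition 12%. 1:1 allocation is assumed. A two-sample t-test needs 64 per arm, 128 in total. 128 / (1 − 0.12) = 145.5, rounded up to 146. The stated sample size is reproduced and this point does not affect it. It supplies the yardstick (0.5 SD) and the number of completers (64 per arm).

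**3. Illustrative size of a recording difference**

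Assumptions, none of them trial data:

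- Equal true activity in both arms, mean 7000 steps/day. This borrows the walking target in the self-monitoring section; it is not an expected mean.
- SD of 2500 to 4000 steps.
- L = share of steps that controls lose to non-wear or misuse beyond what NeCR loses.

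Spurious difference in SD units = L × 7000 / SD.

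| L | Steps/day | SD 2500 | SD 4000 | Share of 0.5 |
|---|---|---|---|---|
| 0% | 0 | 0 | 0 | 0% |
| 5% | 350 | 350/2500 = 0.14 | 350/4000 = 0.09 | 18% to 28% |
| 10% | 700 | 700/2500 = 0.28 | 700/4000 = 0.18 | 35% to 56% |

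**4. Effect on the chance of a false finding for NeCR**

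With 64 completers per arm, the standard error in SD units is √(2/64) = 0.177. The chance of a significant result favouring NeCR with no true effect is Φ(bias/0.177 − 1.96).

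- L = 0%: Φ(−1.96) = 2.5%, the nominal value.
- L = 5%: Φ(−1.47) to Φ(−1.17), or 7% to 12%.
- L = 10%: Φ(−0.97) to Φ(−0.38), or 17% to 35%.

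These figures treat the step count as a simple two-group comparison at one time point.

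**The case against.** The strongest reply is that much of the contrast comes from unequal detail in a condensed article. Usual care gets two sentences and the intervention several sections. The control sentence does not say that instruction is all controls receive, and it does not rule out a leaflet or practice. It shows that the authors deliberately provided device training for controls. The return-demonstration sentence also closes a paragraph that covers the web platform as well as the pedometer, so it may not be specific to the band, although it directly follows the pedometer sentence. All of this stands, and it is why the point is about handling as described.

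Four stronger readings are tempting, and the documents do not support them:

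- *NeCR participants are prompted to wear the band and controls are not.* The reminders are to upload data. Uploading a daily count presupposes wearing the band, but a wear prompt is an inference.
- *A control who takes the band off is scored as inactive.* No rule for non-wear is stated. A band off for part of a day would lower that day's count, no more than that.
- *The pedometer is the plan's safeguard against social desirability bias.* The limitations section says that self-reports may be subject to that bias. It gives the pedometer no such role.
- *The absence of a wear-time rule is itself an error.* Such a rule may well sit in the full protocol or analysis plan, which are not shown.

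It is also fair to say that self-monitoring with step feedback is part of NeCR, so a real rise in walking from it is the effect under study. That narrows the concern to differential recording but does not remove it.

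**Conclusion.** The point holds as a matter of trial conduct. The instrument for the only objective primary measure is also an intervention component, and the training and follow-up described around it are fuller in NeCR. Arm-dependent recording could therefore be read as a step-count benefit.

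The size cannot be established from the documents, and neither can the existence of any excess control loss; if there is none, there is no bias. Under the stated assumptions, a loss of 5% to 10% would give roughly 0.09 to 0.28 SD. That is large enough against a planning effect of 0.5 to justify a cheap precaution, but it is not an estimate for this trial. The other primary measures and the sample size of 146 are unaffected. The change should be made before data collection, because steps that were never recorded cannot be recovered in the analysis.

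**What to change.** Separate measurement from intervention, leaving the NeCR upload prompts and feedback as they are:

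1. Give both arms the same written instructions for the band and the same practice with return demonstration, and say so under Usual care.
2. Send both arms the same neutral wear reminder just before the three-weekday windows at T1 and T2.
3. Apply one valid-day criterion to both arms, and report the number of valid days by arm. If the full protocol already has such a rule, only this third item is redundant.

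The cost is a few extra minutes of training per control participant, one message per visit and a check of wear on the recorded days. Some days may become invalid, and the reminder may slightly raise control wear.

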### Study sample

The study will be conducted at four cardiology units of Tongji Hospital, Wuhan, China where CHD patients are treated conservatively with percutaneous coronary intervention (PCI) or medication and discharged under stable medication regimen. Eligibility requirements of participants are: adults aged 18 years or older; hospitalized for an initial diagnosis of CHD based on angiography or exacerbation of this condition in previously diagnosed cases; anticipated discharge to home; uses a computer and/or smartphone to access the Internet at home, reads and speaks Mandarin; minimum of primary education level; and no prescribed activity or exercise restriction. Exclusion criteria are: a diagnosis of acute psychotic disease/ life-limiting condition; absolute and relative contradictions to exercise testing and training and high risk for exercise prescription according to the American Association of Cardiovascular and Pulmonary Rehabilitation (AACVPR) guideline; and, having auditory, visual, fine motor, or ambulatory disorders.

Referring to a systematic review of studies which examined the effects of tele-cardiac rehabilitation on lifestyle behaviors, health outcomes and quality of life, the effects size on promoting healthy lifestyle is 0.42 to 1.29 so that a medium effect size of 0.5 (with 80% power and .05 significance) is conservatively adopted in this study [38]. The estimated sample size is 146, which takes into consideration an expected attrition rate of 12% based on prior studies with similar post-test time points of 6–12 weeks [31, 39]. Eligible participants will be identified by research nurses from four inpatient cardiac departments of the hospital by reviewing medical records. A second confirmation will be made with the on-site physicians. Eligible participants will then be invited to participate in this study and an information sheet will be provided. After obtaining informed consent, baseline data will be collected.

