### Data analysis

The latest version of SPSS will be used to analyze data with a 5% significance level (two-sided). Treatment evaluation will be performed based on the principle of intention to treat. A generalized estimating equations (GEE) model will be used to compare the differential between the two groups related to each of the outcomes across the time-points, with adjustment for potential confounding variables in order to obtain a more precise estimation of intervention effect. The potential confounding variables will be selected on the basis of clinical judgment and statistical incomparability at baseline. For the smoking behavior as nominal data, the Chi-square test will be used to compare the number of patients who quit smoking between the groups. In addition, the Friedman test will be used to compare the changes in percentage of smoking cessation among the groups over time [73]. Survival analysis, the analysis of time-to-event data will be conducted to describe the length of time from entering the program to an unplanned health services utilization.

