## Discussion

This study will use a hybrid approach guided by an empowerment model to investigate the effect of eHealth CR which integrates behavior change strategies on not only exercise but also on diet, stress and smoking. The intervention content and web-design are based on international guidelines and national culturally appropriate recommendations to improve credibility, comprehensibility and implementation for this population. Individual assessment and a collaborative approach to goal setting and action planning helps participants understand the purpose of using the web- and tele-platform. This could also encourage participants’ engagement in self-care decision making with their health care professional and proactive use of the e-platform, which are resources for self-management. Considering the continuous care needs of a patient discharged to their home setting after a cardiac event, individual consultation and guidance from a nurse and encouragement from peer interaction and support will be initiated through multi-communication channels as social motivators for behavioral goal attainment. This study uses a new method of peer support in which the researcher shares participants’ progress toward goal attainment with the peer group and encourages participants to share their experiences and concerns to reinforce behavioral changes.

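### Peer groups exist only in the NeCR arm, but the sample size and the stated GEE treat participants as independent; if outcomes correlate within groups, standard errors will be too small and 80% power too high

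*Protocol article*

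**What the plan says.** Under Face-to-face preparatory phase, the NeCR arm attends an engagement session of 4 to 6 people. One of its aims is to "form a cohesive peer support group to optimize lifestyle behavioral changes". Then "the nurse will invite participants to enter a WeChat telecare platform consisting of 12 ~ 16 participant members". Under Tele-care platform, the nurse shares members' goal attainment without names and leads discussion of their experiences. The Discussion presents this as a feature of the trial: "This study uses a new method of peer support in which the researcher shares participants’ progress toward goal attainment" with the peer group. The Usual care section describes no groups.

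Under Study sample, "a medium effect size of 0.5 (with 80% power and .05 significance) is conservatively adopted in this study", and "The estimated sample size is 146, which takes into consideration an expected attrition rate of 12" per cent. No ICC or design effect appears among these inputs.

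Under Data analysis: "A generalized estimating equations (GEE) model will be used to compare the differential between the two groups" on each outcome across the time points, adjusted for confounders, at a two-sided 5% level. Neither peer group nor session is named as a level of the model.

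**The concern.** The groups are meant to make members influence one another, and the primary outcomes (activity, lifestyle habits, smoking) are the behaviours they are meant to shift. Patients sharing a group may therefore end up more alike than patients in different groups. This is a partially nested trial: clustered in one arm, unclustered in the other.

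A GEE with the patient as subject allows for correlation between a patient's own visits. Its robust standard error does not capture correlation between different patients. If that correlation is positive, confidence intervals for the NeCR effect are too narrow, p-values are too small, and the planned power is optimistic.

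**Working it through.** **Inputs from the protocol article.** Effect size 0.5 (so SD = 1), 80% power, 5% two-sided, 12% attrition, total 146; sessions of 4-6; WeChat groups of 12-16.

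**Assumed.** 1:1 allocation (the ratio is not stated); ICC of 0.01, 0.02, 0.05 and 0.10 (none is given).

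**1. The plan's own figure.** A two-sample t-test at these inputs needs 64 per arm, 128 in all. 128 / (1 - 0.12) = 145.5, rounded up to 146. This is an exact match, so 146 contains no allowance for clustering.

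**2. Number of groups.** 146/2 = 73 NeCR patients. 73/16 = 4.6 and 73/12 = 6.1, so about five or six WeChat groups. With 64 analysed, the mean group size is 64/5 = 12.8 or 64/6 = 10.7.

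**3. Standard error.** For mean group size m, the design effect is DE = 1 + (m - 1) × ICC, in the NeCR arm only. With equal arms, the true SE divided by the independence SE is √((1 + DE)/2), and the actual size of a nominal 5% test is 2 × [1 - Φ(1.96 / SE ratio)].

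At ICC 0.05:
- Five groups: DE = 1 + 11.8 × 0.05 = 1.59; SE ratio = √1.295 = 1.138; 1.96/1.138 = 1.72; size about 8.5%.
- Six groups: DE = 1 + 9.7 × 0.05 = 1.48; SE ratio = √1.24 = 1.114; 1.96/1.114 = 1.76; size about 7.9%.

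**4. Simulation.** 64 controls and 64 NeCR patients in six or five WeChat groups. The analysis ignoring groups is a t-test. The analysis respecting them compares group means with controls, using Satterthwaite degrees of freedom.

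| ICC | Type I error, groups ignored | Power at 0.5, groups respected |
|---|---|---|
| 0 | 5% | 75-76% |
| 0.01 | 5.3-5.9% | 72-73% |
| 0.02 | 6.0-6.4% | 69-71% |
| 0.05 | 7.7-8.6% | 61-65% |
| 0.10 | 10.8-12.3% | 52-56% |

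A check run of 40,000 trials per setting came within about 0.3 percentage points of these sizes and 1 point of these powers.

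**5. Splitting the power loss.** With five or six groups, power is already about 75-76% at an ICC of zero, because few degrees of freedom remain. Roughly 4 to 5 points of the drop from 80% are therefore due to the small number of groups. Only the further fall down the table is due to correlation.

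**6. If only the sessions cluster.** With sessions of about five and the same ICC range, size runs from 5.3% to 7.3% and power from 78% to 71%.

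**The case against.** The ICC is unknown and could be small. Much of NeCR is individual: one-to-one counselling, personal goals, a personal web page with automated feedback, and nurse contact at weeks 2 and 4. Sharing in the group is anonymous. At an ICC of 0.01, or if only the sessions cluster, the distortion is minor. This stands, so the point has to be conditional. Anonymity does not remove shared discussion and feedback, though, and a correlation of zero would sit badly with the mechanism the trial relies on.

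The Data analysis section is also a condensed paragraph, and an analysis plan that is not shown could add a group term. This stands in part: nobody can say that peer group will be ignored. But the sample size is fixed in the text and rests on independence, the model is described for time points only, and group membership has to be captured during delivery.

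Three stronger readings are tempting and not supported:
- **The standard errors are too small as a matter of fact.** This needs a positive ICC, which the document does not give.
- **The error favours NeCR.** The inflation is two-sided. It also needs variation between groups with zero average effect; if NeCR changed nothing for anyone, peer exchange would create no correlation.
- **80% power would hold if the ICC were zero.** That is true of the independent-participant t-test, not of an analysis that respects five or six groups.

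**Conclusion.** The point holds conditionally. The design is partially nested, 146 carries no allowance for that, and the stated model has no group level. If the within-group correlation is positive, the planned analysis is anti-conservative and 80% overstates the power of a valid one.

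The distortion is slight at an ICC of 0.01 and material from about 0.05, where size is about 8% and group-respecting power 61-65%. These figures rest on the assumed ICC range, 1:1 allocation, 64 analysed per arm, clustering at WeChat level and a single time point. The power figures come from a group-mean analysis, so they approximate what a repeated-measures mixed model would give. The matter should be corrected, but it does not invalidate the trial.

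**What to change.** - Record the WeChat group and engagement session of every NeCR participant as data fields.
- Analyse continuous outcomes with a partially nested mixed model: a random group intercept in the NeCR arm only, repeated measures within participant in both arms, and Satterthwaite degrees of freedom. Five or six groups are too few for an uncorrected cluster-robust GEE.
- Report the estimated ICC.
- In Study sample, state that 80% is the power of a t-test on independent participants, and give the range above for the group-respecting analysis. Do not write that 80% holds at an ICC of zero.

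The cost is two data fields and some wording, with no extra patients. The price is wider confidence intervals and a lower stated power.
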